# Efficacy of i-PRF in regenerative endodontics therapy for mature permanent teeth with pulp necrosis: study protocol for a multicentre randomised controlled trial

**DOI:** 10.1186/s13063-021-05401-7

**Published:** 2021-07-06

**Keywords:** Dental pulp necrosis, Regenerative endodontics therapy, Pulp regeneration, Blood clot, Injectable platelet-rich fibrin, Mature permanent teeth

## Abstract

**Background:**

Dental pulp necrosis, a common health problem, is traditionally treated with root canal therapy; however, it fails in restoring the vitality of damaged pulp. Most studies regarding regenerative endodontic therapy (RET) are limited to the treatment of immature necrotic teeth. Given that injectable platelet-rich fibrin (i-PRF) has shown great potential in regenerative medicine as a novel platelet concentration, this study is designed to explore whether i-PRF can serve as a biological scaffold, extending the indications for RET and improving the clinical feasibility of RET in mature permanent teeth with pulp necrosis.

**Methods:**

This is a randomised, double-blind, controlled, multicentre clinical trial designed to evaluate the clinical feasibility of RET for mature permanent teeth with pulp necrosis and to compare the efficacy of i-PRF and blood clots as scaffolds in RET. A total of 346 patients will be recruited from three centres and randomised at an allocation ratio of 1:1 to receive RET with either a blood clot or i-PRF. The changes in subjective symptoms, clinical examinations, and imaging examinations will be tracked longitudinally for a period of 24 months. The primary outcome is the success rate of RET after 24 months. The secondary outcome is the change in pulp vitality measured via thermal and electric pulp tests. In addition, the incidence of adverse events such as discolouration, reinfection, and root resorption will be recorded for a safety evaluation.

**Discussion:**

This study will evaluate the clinical feasibility of RET in mature permanent teeth with pulp necrosis, providing information regarding the efficacy, benefits, and safety of RET with i-PRF. These results may contribute to changes in the treatment of pulp necrosis in mature permanent teeth and reveal the potential of i-PRF as a novel biological scaffold for RET.

**Trial registration:**

ClinicalTrials.govNCT04313010. Registered on 19 March 2020

**Supplementary Information:**

The online version contains supplementary material available at 10.1186/s13063-021-05401-7.

## Background

Dental pulp necrosis has become one of the most common health problems being the sequelae of caries, trauma, and inappropriate endodontic treatments [1, 2]. Necrosis of the dental pulp not only affects long-term tooth survival and preservation, but also can serve as a source of bacteria leading to the infection of periapical tissue and even the maxillofacial space. In addition, there is a strong correlation between oral infections and systemic diseases such as cardiovascular diseases and diabetes mellitus [3].

To date, root canal therapy (RCT) is the most acceptable treatment for pulp necrosis, based on the replacement of inflamed or necrotic pulp tissue with artificial filling materials [4]. However, this conventional therapy does not restore the vitality of damaged pulp or reconstitute the neurovascular system [5, 6]. Therefore, regenerative endodontic therapy (RET) has attracted increasing attention with the development of tissue engineering. RET applies the concept of tissue engineering (stem cells, biomimetic scaffolds, and bioactive growth factors) to achieve revascularization, innervation, and restoration of odontoblastic layers [5, 7, 8]. Unlike root canal therapy, the disinfected canals are filled with vital tissue in RET rather than biocompatible, nonvital foreign materials [9]. While several studies have explored the potential of pulp regeneration for infected teeth, most studies are limited to the treatment of immature necrotic teeth [10]. For mature permanent teeth, vital pulp is also of great importance in enhancing the immune system in root canals, promoting dentin deposition under chronic stimuli, and preventing discolouration [6]. But most of the reports of pulp regeneration in mature teeth are case reports or case series [6, 9, 11, 12] as mature teeth have fewer stem/progenitor cells, have narrower apical pathways for cell migration, and are more difficult to disinfect [4, 6, 13]. Hence, it is of great urgency to develop an improved RET procedure to maximise the regeneration potential of mature teeth and extend the indications of RET.

Scaffolds play a key role in RET, as they provide a favourable microenvironment for stem cells to migrate, proliferate, and differentiate [14–17]. Blood clot revascularization (BCR) is the most common revascularization method, in which the blood clot can serve as a scaffold and is formed by an endodontic file introduced into the root canal beyond the apical foramen to provoke bleeding from the periapical tissue [13, 18–20]. The evoked-bleeding technique stimulates surviving dental pulp stem cells near the root apex to migrate into the root canal space, such as periodontal ligament stem cells and bone marrow mesenchymal stem cells [6, 21, 22]. However, blood clots are a poor source of growth factors [19], and the precise technique required to control the speed and volume of bleeding has limited its applications in clinical practice [20]. Furthermore, several studies regarding mature necrotic teeth reported that BCR resulted in a negative response to pulp sensibility after 8–26 months [23]. Therefore, the development of a bioscaffold with high concentration of pro-regenerative factors is an important topic in the field of pulp regeneration.

Platelet products have been used in tissue regeneration and dentistry for over two decades and have shown great potential in providing an optimal scaffold for pulp regeneration [24–27]. Platelet-rich fibrin (PRF), the second-generation platelet concentrate, is a kind of purely natural autologous fibrin matrix with trapped platelets and leukocytes, guaranteeing the prolonged release of growth factors and cytokines [19, 28, 29]. However, the solid-state of PRF limits its applications [30]. There is controversy regarding the performance of PRF in RET compared to that of the conventional blood clots and the first-generation platelet concentrate, platelet-rich plasma (PRP) [17, 20]. As the low-speed centrifugation concept (LSCC) was developed, injectable platelet-rich fibrin (i-PRF) was developed as a novel liquid blood derivative in 2014. This liquid blood derivative is enriched with high concentrations of platelets, leukocytes, and growth factors [31–33]. Recent studies have reported that i-PRF provides a three-dimensional fibrin-dynamic gel embedded with platelets, leukocytes, type-I collagen, osteocalcin, and growth factors [31] with the potential to modulate inflammatory processes [34], exert anti-bacterium and anti-biofilm activities [35, 36], and promote osteogenesis [37–39]. Compared to PRF, i-PRF results in better bone regeneration [39], treatment of gingival recession defects [40], and elimination of endodontic infection [36]. However, there is no high-quality evidence regarding whether i-PRF, as an improved platelet product, could serve as an optimised scaffold in RET. At the same time, the lack of a standard protocol for RET with i-PRF also limits the use of i-PRF in RET, as different protocols may result in different treatment outcomes [5, 41, 42].

Therefore, the main aim of this randomised, double-blind, controlled, multicentre clinical trial is further evaluating the efficacy of RET in treating mature necrotic teeth, and exploring the feasibility of i-PRF as a scaffold in RET.

## Methods

### Study design and objectives

This is a randomised, double-blind, parallel positive control, multicentre clinical trial (Fig. 1) that aims to compare the efficacy of i-PRF and blood clots (BCs) as scaffolds in RET for mature permanent teeth with pulp necrosis. The protocol will be reported according to the Standard Protocol Items: Recommendations for Interventional Trials (SPIRIT) statement (Additional file 1). After informed consent acquisition, all eligible patients (*n* = 346) will be randomly divided into two groups at an allocation ratio of 1:1. Patients in the test group will receive RET with i-PRF while those in the control group will receive conventional RET with BC. The follow-up period will be 24 months, and clinical data will be collected at 1, 3, 6, 12, 18, and 24 months after surgery. Figure 2 outlines the schedule of events for patients in the trial.

**Fig. 1 Fig1:**
[figure not shown]
Study flowchart

**Fig. 2 Fig2:**
[figure not shown]
Schedule of intervention and assessments. All study-related procedures are outlined in this figure. RET, regenerative endodontic therapy; CBCT, cone beam computed tomography

The primary objective of this study is to evaluate the efficacy of RET and RET with i-PRF for the treatment of mature permanent teeth with pulp necrosis. The secondary aim is to carefully investigate the factors influencing the clinical outcomes of RET in mature permanent teeth with pulp necrosis, and at the same time, to explore the standard RET protocol for treating mature permanent teeth with pulp necrosis.

### Study setting and recruitment

The study will be carried out at three centres of Southern Medical University: NanFang Hospital, Stomatological Hospital, and Shenzhen Hospital. Two dentists from each centre will participate in this trial after receiving standardised training to obtain a comprehensive overview of the rationale and strategy of the standard intervention procedure. A total of 346 patients will be recruited via outpatient hospital clinics by researchers of the above centres. After an eligibility assessment and informed consent, the patients will be randomly assigned to the control group or the experimental group at a ratio of 1:1. Patients who agree to participate in this study will sign an informed consent form.

#### Inclusion criteria

Agree to participate in this study and provide informed consentAge 10–59 years at the time of enrolmentAt least one mature permanent tooth diagnosed with pulp necrosis (no response to pulp vital test) with or without periapical lesionsRadiologic confirmation (cone beam CT (CBCT)) of a single root necrotic tooth with a single root canal

#### Exclusion criteria

Teeth with severe coronal defects that require post and core as final restorationsNon-restorable teethTeeth with root fractures or split rootsPresence of other pathological root resorptionsPresence of periodontitisAllergies to any medications or materials necessary to complete the proceduresPresence of dental dysplasia or other oral genetic disordersWomen who are pregnant or lactating, or women who plan to become pregnant in the subsequent 2 yearsPresence of dental phobiaPresence of mental disordersA history of systemic diseases that may alter immune functionMedical conditions and/or receiving medications that affect healing or blood coagulationParticipation in other clinical studies within the past 3 monthsPatients who are deemed unsuitable to participate in the study by investigators

#### Dropout criteria

Presence of serious adverse events that doctors believe should lead to termination of trial participation, such as severe internal or external root resorption and tooth fracturePoor clinical complianceWithdrawal of consent for study participation by the patient

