#### Primary outcome measures

The therapeutic effect evaluation criteria are the following:
*Success*. After RET, the tooth is asymptomatic, with an absence of percussion pain, bone adhesion percussion sound, loosening, tenderness, mucosal swelling, sinus, or fistula. The radiographic examination demonstrates the absence of an apical shadow or a reduced apical shadow.*Failure*. After RET, the tooth is symptomatic, with symptoms of apical infection such as pain and fistula. The radiographic examination demonstrates a new-onset apical shadow or an enlarged apical shadow.

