#### Statistical analysis

The data will be analysed by an independent statistician using SPSS 20.0 software (IBM Co., Armonk, NY, USA) at the end of the study to evaluate the evolution. The continuous variables will be described as the mean (standard deviation) or median and analysed using parametric methods. Categorical variables will be described as percentages and analysed using non-parametric methods. The level of significance will be *P* < 0.05, and 95% confidence intervals will be calculated.
*Baseline analysis*

The two groups will be comparable in terms of sex, age, tooth position, disease type, and apical hole size. Quantitative variables will be analysed using a one-way analysis of variance (independent sample t-test) or non-parametric methods if the data do not meet and cannot be transformed to meet parametric assumptions. Qualitative variables will be analysed using the Wilcoxon rank-sum test. A principal component analysis will be performed using multinomial logistic regression to adjust for potential confounders.
(2)*Main outcome analysis*

The inter-group comparison of success rates will be analysed using the chi-square test. If there are baseline variables influencing the comparability of the two groups, a logistic regression model will be used to eliminate the effects of these confounders on the success rate and the odds ratio (OR) will be calculated. For the missing data, the last observation carry forward method will be adopted to fill the validity analysis, that is, the case data that fails to observe the whole treatment process will be transferred to the final result of the test with the last observation data.
(3)*Secondary outcome analysis*

For intra-group comparisons, McNemar’s test will be used to analyse the clinical outcomes of different centres. For inter-group comparisons, the secondary outcome will be analysed using the Chi-square test.
(4)*Safety evaluation analysis*

The adverse events that occur during the study period will be listed for each group and compared using the chi-square test. The security evaluation does not evaluate missing data.

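### A tooth that leaves the trial for severe root resorption or fracture can still count as a 24-month success

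*Protocol article*

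**What the plan says.** Four parts of the protocol article bear on this.

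- **Dropout criteria.** Participation ends for "serious adverse events that doctors believe should lead to termination of trial participation, such as severe internal or external root resorption"; tooth fracture is the other example given.
- **Primary outcome measures.** Success has a clinical part, "the tooth is asymptomatic, with an absence of percussion pain, bone adhesion percussion sound, loosening, tenderness, mucosal swelling, sinus, or fistula", and a radiographic part, "The radiographic examination demonstrates the absence of an apical shadow or a reduced apical shadow". Failure means "the tooth is symptomatic, with symptoms of apical infection such as pain and fistula", and on imaging, "The radiographic examination demonstrates a new-onset apical shadow or an enlarged apical shadow". Resorption and fracture appear in neither definition.
- **Statistical analysis, main outcome.** Last observation carried forward (LOCF) applies to efficacy: "the case data that fails to observe the whole treatment process will be transferred to the final result of the test with the last observation". No exception is made for teeth that leave because of an adverse event.
- **Safety evaluation.** Internal and external root resorption are listed among the adverse events that RET may cause.

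The endpoint is the success rate at 24 months. Visits are at 1, 3, 6, 12, 18 and 24 months (Outcome measures).

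**The concern.** Severe resorption and fracture are bad results for the treated tooth, and the protocol itself regards resorption as a possible effect of RET. Exits for these reasons are informative. The plan nevertheless handles them as ordinary incomplete follow-up, and the value it fills in may predate the event.

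An arm that causes more of these events can then gain in the primary outcome from each one. Another imputation method would not cure this by itself. A method that assumes data are missing at random would fill in these teeth as if they resembled comparable teeth still under observation, although the reason for exit is known.

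**Working it through.** **1. Reading the rules together.** Take a tooth that is symptom-free with a reduced apical shadow at 12 months and leaves for severe resorption before the 18-month visit.

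- Dropout criteria: participation may end, so there is no 24-month observation.
- Primary outcome measures: the event that ended participation is not a criterion of Failure.
- Main outcome analysis: the 12-month value, a success, becomes the final result.

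The gap also exists without imputation. An asymptomatic tooth with severe resorption, none of the listed signs and no new or enlarged apical shadow meets the Success definition at the visit itself.

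**2. The plan's own figure.** Sample size gives 346 (173 per group) at α = 0.05 and 80% power, but no success rates or difference. The figure can be neither reproduced nor refuted, and this point does not depend on it. For scale, at 173 per arm, two-sided 0.05 and 80% power, the detectable improvement from 80% is 10.6 points.

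**3. Size of the shift.** Let k be the number of such teeth carried as success in an arm of n = 173. If they ought to be failures, the arm's success rate rises by k/n, and the between-arm difference moves by (k₁ − k₂)/n.

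Assumption: true success is 80% in both arms, so any significant result is false. With observed rates p₁ and p₂, Δ = |p₁ − p₂|, s₀ = √(2p̄(1−p̄)/n) and s₁ = √(p₁(1−p₁)/n + p₂(1−p₂)/n):

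P(reject) = Φ((Δ − 1.96 s₀)/s₁) + Φ((−Δ − 1.96 s₀)/s₁)

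| Teeth carried as success | Observed rates | Shift (points) | P(reject) |
|---|---|---|---|
| 0 v 0 | 80.0% v 80.0% | 0 | 5% |
| 4 v 2 | 82.3% v 81.2% | 1.2 | about 6% |
| 7 v 3.5 | 84.0% v 82.0% | 2.0 | about 8% |
| 14 v 7 | 88.1% v 84.0% | 4.0 | about 19% |

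For 14 v 7: 7/173 = 4.0 points and s₀ ≈ s₁ ≈ 0.0372, so (0.0405 − 0.0729)/0.0372 ≈ −0.87 and Φ ≈ 0.19; the other tail adds 0.001. The 7 v 3.5 row is 14 v 7 events with half, on average, successful at the last visit.

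**4. A different assumption.** The table fixes total failures at 20% in both arms, so the arm with more resorption and fracture must have fewer other failures. Suppose instead that other failures are 16% in each arm and these events are 8% v 4%. True success is 100 − 16 − 8 = 76% against 100 − 16 − 4 = 80%. With every such tooth carried as success, the observed rates are 84% v 84%. The real 4-point disadvantage disappears and rejection is 5%.

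**5. Equal rates.** If the proportion carried as success is the same in both arms, both rates are too high but the difference is unchanged: with 5% in each, 80% v 90% becomes 85% v 95%, still 10 points.

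**The case against.** Several objections limit the point, and they stand as limits.

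- **The carried value is not always a success.** A reader might infer that every such tooth is scored as a success. LOCF carries whatever was last seen, so a tooth already failing is carried as a failure. The protocol also does not say whether the visit that finds the event is the last observation. If it is, a painful or loose fractured tooth, or one with a bone-adhesion percussion sound, does not meet Success. The text supports *can be*, not *is*. An asymptomatic tooth with severe resorption still passes on either reading.
- **The teeth are not excluded from the analysis.** It is participation that ends. LOCF keeps them in the efficacy comparison, so the fault is in their classification.
- **Safety.** The sentence "The security evaluation does not evaluate missing data" might suggest that events after exit are ignored. It reads more naturally as no imputation for safety data. Adverse events are recorded in detail and compared between groups, so the triggering event stays visible there.
- **Who decides.** A reader might infer that unblinded treating dentists choose who leaves. The dropout criteria say only doctors. The dentists who perform the treatment are unblinded, but the text does not equate the two. Nor do the documents show that the separate compliance criterion causes this problem.
- **Event rates.** None are given. The 14 v 7 case needs 14 of one arm's 34.6 failures (20% of 173), about 40%, to be such exits, all carried as success. With few events the distortion is small.

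None of this supplies the missing classification. The dropout rule, both outcome definitions and the imputation rule are all stated in the protocol, so this is not a detail left to an analysis plan.

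**Conclusion.** The concern holds in this form: the stated rules allow a tooth that leaves for severe resorption or fracture to count as a 24-month success, through LOCF or, if it is asymptomatic with no apical change, through the Success definition alone. Each such tooth raises its arm's success rate by 1/173, about 0.6 points, and the difference moves towards the arm with more of them.

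The direction follows from the rules; the size rests on assumed rates. It runs from about 6% false rejection (4 v 2 teeth) to about 19% (14 v 7) when true success is equal at 80%. If other failures are equal, the error is a hidden difference (76% v 80% seen as 84% v 84%). A shift of up to 4 points matters against a detectable difference of about 10.6 points.

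**What to change.** State in both the primary outcome definition and the missing-data rule that a tooth whose participation ends because of a tooth-related adverse event (severe resorption, fracture) is classed as Failure at 24 months. Keep LOCF for these teeth only as a sensitivity analysis. Continue to collect outcome and safety data to 24 months wherever consent has not been withdrawn. Reconcile Dropout criteria, Primary outcome measures, Safety evaluation and Statistical analysis accordingly. The clinical decision to stop is left as it is.

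The cost is protocol wording, the extra follow-up of these patients, and slightly lower reported success rates.

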### Randomisation, allocation, and blinding

Eligible patients will be randomly assigned to one of two groups at an allocation ratio of 1:1. The randomisation sequence and grouping will be generated and stored by one researcher who will not be involved directly in participant screening, enrolment, or assessment, using SPSS 20.0 software (IBM Co., Armonk, NY, USA). All random numbers will be listed sequentially, and a set of 10 numbers will be arranged as a cluster (the first 5 for the test group and the last 5 for the control group). Then, random numbers and grouping are inserted in opaque and sealed envelopes sequentially. After all the envelopes have been sealed, they will be distributed to each research centre. Only dentists can open the envelope to check the group allocation and perform the interventions according to the instructions of this study. As a double-blind trial, the patients and outcome evaluators will be blinded to the group assignment until the completion of the study. As dentists cannot be blinded to treatment allocation due to the notable differences in the treatment methods, they will not be allowed to discuss the type of intervention with either patients or outcome evaluators.

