### Sample size and statistical methods

#### Sample size

The primary outcome measure is the success rate at 24 months after treatment. According to nQuery Advenced 8.6 software (Statistical Solutions Ltd., Cork, Ireland), a sample size of 346 (173 for each group) patients is required when α = 0.05 and the test power is 80%.

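### As written, the block rule sets the arm by list position, so the sequence is not random and the unblinded dentists can predict it

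*Protocol article*

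**What the plan says.** The article's section on randomisation, allocation and blinding opens with the aim: "Eligible patients will be randomly assigned to one of two groups at an allocation ratio of 1:1". A researcher outside screening, enrolment and assessment generates and holds the sequence, using SPSS. The mechanics follow in three steps:

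- "All random numbers will be listed sequentially".
- The list is cut into tens: "10 numbers will be arranged as a cluster (the first 5 for the test group and the last 5 for the control group".
- The envelopes are filled in list order: "random numbers and grouping are inserted in opaque and sealed envelopes sequentially".

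The envelopes are then sent to the three centres. On who opens them, the section says: "Only dentists can open the envelope to check the group allocation and perform the interventions". It also concedes that these operators are unblinded: "As dentists cannot be blinded to treatment allocation due to the notable differences in the treatment methods". Patients and outcome evaluators are blinded.

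Two other sections matter. Study setting and recruitment puts two dentists at each centre and has researchers of the centres recruit; it does not say whether these are different people. The last exclusion criterion lets investigators exclude anyone they judge unsuitable.

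**The concern.** In a permuted block, chance decides the order of arms within the block. Here the arm follows from the position in a list, and the envelopes keep that position. The random numbers then decide nothing.

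Opaque sealed envelopes hide the content of a single envelope but not a repeating pattern. The people who see each allocation are the treating dentists, and the block size and rule stand in a public article issued while, according to the Trial status section, patients were being recruited.

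Selection bias in the primary comparison is at stake. Teeth enter with or without periapical lesions, and success at 24 months depends partly on the apical shadow. Anyone who can foresee the next arm and has a say in whether or when a patient is enrolled could, knowingly or not, send more favourable teeth to one arm. The discretionary exclusion gives room for this.

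**Working it through.** **Inputs.** All come from the randomisation section: 1:1 ratio, fixed blocks of 10, positions 1–5 to test and 6–10 to control, envelopes filled in list order, no ranking or permuting step stated. The total of 346 comes from the Sample size section.

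**1. The plan's own ratio.** Each complete block gives 5 test and 5 control, so the rule meets 1:1 block by block. The derivation of the 346 cannot be checked, because the article gives no success rates. Nothing here depends on it.

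**2. Literal reading.** Writing T for test and C for control:

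- Number of possible orders per block: 1, namely TTTTTCCCCC.
- Number of orders if the block were randomly permuted: C(10,5) = 252.
- Allocations predictable once the rule, or one complete block, is known: 10 of 10, or 100%.

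**3. Ranked reading.** Suppose the five lowest random numbers in each ten go to test and the envelopes stay in the order in which the numbers were generated. All 252 orders are then equally likely and the sequence is random. What remains is the predictability of a fixed block size.

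Take an observer who knows where blocks start and has seen every earlier allocation. The best strategy is to guess the arm with more places left, and to toss a coin when they are equal. For a block of size 2m:

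- Expected correct guesses = m + (4^m / C(2m, m) − 1) / 2.
- With m = 5: 5 + (1024/252 − 1)/2 = 5 + (4.063 − 1)/2 = 6.53 of 10, or 65.3%.

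An allocation is certain once one arm is used up within the block:

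- Expected number certain = 2m/(m + 1) = 10/6 = 1.67 of 10, or 16.7%.

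A simulation of 40,000 blocks gave 65.3% correct and 16.6% certain, in agreement with the formulas.

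**4. Comparison.**

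| Scheme | Correct guesses | Certain |
|---|---|---|
| Rule as written | 100% | 100% |
| Permuted, fixed block of 10, size and boundaries known | 65.3% | 16.7% |
| Simple randomisation | 50% | 0% |

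**5. Would a smaller fixed block help?** No. If the size is known, the same formula gives 2.83 of 4 (70.8%) for blocks of four and 4.1 of 6 (68.3%) for blocks of six. Protection has to come from sizes that vary and are not disclosed.

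**The case against.** The strongest objection is that the literal reading cannot be what the authors meant. If position alone set the arm, there would be no reason to generate random numbers or to put them in the envelopes. Listing numbers in sequence may mean sorting them by size, with the lower five going to test, and a condensed article may have dropped a step. This is a fair point, and it means that the text does not show what was actually done. It does not rescue the wording. The article states a specific rule, not merely an abbreviated one, and that rule contains no ranking. Sorting helps only if the envelopes then return to the order in which the numbers were generated; if they follow the sorted list, each block is again five test then five control.

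Two further objections stand in part. The article does not say that the treating dentists enrol patients, and it places assignment after eligibility assessment and consent. Steering is therefore a risk and not a demonstrated event. The 65% figure also needs an observer with full knowledge: nothing says that the two dentists at a centre see each other's allocations, and the division of envelopes between centres is not described, so blocks may not be intact at a site.

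The Statistical analysis section would compare the arms on disease type and apical hole size, and would use logistic regression if baseline variables affect comparability. That can address measured imbalance. It cannot address selection on clinical impression or other unrecorded features.

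A reader might also infer two stronger things that the article does not support:

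- **Arm is confounded with calendar time or operator learning.** Under the literal rule the arms alternate every five patients. Mean position within a block is 3 for test and 8 for control, a gap of 5 places, or 5/346 = 1.4% of a single list. Over 34 complete blocks calendar time is nearly balanced.
- **The rule breaks the stated 173 per group.** One list of 346 has 34 complete blocks plus 6 patients, hence 170 + 5 = 175 test and 170 + 1 = 171 control. Any blocked list can stop in mid-block, the difference is immaterial, and blocks of varying size would not guarantee 173 each either.

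**Conclusion.** The point holds as a defect in the stated rule. Followed as written, allocation is deterministic and 100% predictable to the unblinded dentists who open the envelopes. If the ranked reading was intended, the sequence is random, but a fixed and published block of ten leaves about 65% of allocations guessable and about 17% certain for an observer who knows the block boundaries and all earlier allocations.

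The text needs correction under either reading; how serious the matter is depends on how the list was built. A reader might conclude that the trial was not randomised or that its primary comparison is already biased. The article does not support that: it shows a rule and an opportunity, not the list used or any steering. What can be said is that there is a risk of selection bias, with recruitment not separated from the operators and discretionary exclusion allowed, and that the planned adjustment covers only what is measured.

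**What to change.** First, have the independent researcher check the generation record and the existing list, and state in the protocol how the order within each block was obtained.

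Second, whatever the answer, replace the rule for all unused envelopes. Use a computer-generated list of randomly permuted blocks of varying size, stratified by centre. Keep the sizes out of the published text and the centres' documents, and let only the independent researcher hold them.

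Third, only if the literal rule was used: disclose this, flag the patients allocated under it, and add a sensitivity analysis of 24-month success that excludes them. If the numbers were ranked, that analysis should not be added, since it would discard validly randomised patients.

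The cost is a protocol amendment, a new list and re-packed envelopes. No extra patients or study procedures are needed. If the sensitivity analysis is required, it will have less precision, the more so the later the change is made.
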